#### Sample size calculation

The required sample size is calculated using an estimation formula based on the difference between two sample means and standard deviations (Pittsburgh Sleep Quality Index, which is assessed using composite points of sleep quality). A previous clinical study suggests that the mean and standard deviations of Pittsburgh Sleep Quality Index (PSQI) in ARQE group(*n* = 40) after treatment are 8.45 and 2.06, while the mean and standard deviations of PSQI in CBTI group (*n* = 40) after treatment are 9.92 and 2.65 [26, 27]. The sample size is calculated in the following formula, with the two-sided significance level (α) set at 0.05 and statistical power at 0.80 [28]. Thus, a minimum sample size of 51 participants per group (102 participants in total) is calculated to provide sufficient statistical power to detect a between-group mean difference of 1.47 in treatment efficiency, defined as the change in PSQI score.

Considering a 10% loss to follow-up, we aim to recruit 57 patients in each group, in a total of 114 patients. According to fMRI studies, 15 to 30 patients are adequate to test hypotheses.

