### Statistical analysis

#### Primary outcome analysis

With previous set single blind rule, an independent statistician will analyze the clinical data by SPSS V.24.0 statistical software. Data analysis will be based on the intention-to-treat (ITT) principles. The results of ITT analysis will be compared for consistency. A *p* value < 0.05 will be considered statistically significant. Participants who fail to complete the study will be treated as having no change from baseline at all times in both groups. The Kolmogorov–Smirnov test will be used to test the normality. Appropriate transformations will be applied for non-normal distribution, The continuous variables with normal distribution will be described as mean and standard deviation, while continuous variables with non-normal distribution will be expressed by using median and interquartile interval (IQR), the categorical variable will be expressed in number and proportion.

To compare the baseline characteristics between two groups, Student’s *t* test or Mann–Whitney test will be used for continuous variables. Pearson’s *χ*-squared or Fisher’s exact will be used for categorical variables. To compare the primary and secondary outcomes between groups, continuous data will be tested by Student’s *t* test or non-parametric test. Pearson’s *χ*-squared or Fisher’s exact test will be applied for categorical data at baseline and after intervention. Repeated-measures ANOVA using the group-by-time interaction terms will be used to analyze the between-group differences. Multivariate analysis of variance will be used and the two-two comparisons among the changes in questionnaire scores with repeated measurement times for each group will be done by Bonferroni correction.

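### The normality check leaves the two-group PSQI comparison open between a mean, a transformed-mean and a rank comparison, although the trial is sized on a mean difference

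*Protocol article*

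**What the plan says.** All the relevant analysis text is in the protocol article under Primary outcome analysis.

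- A Kolmogorov-Smirnov "test will be used to test the normality".
- "Appropriate transformations will be applied for non-normal distribution". Variables that are not normal are also to be summarised by median and interquartile range.
- The next paragraph turns to testing: "To compare the primary and secondary outcomes between groups, continuous data will be tested by Student’s" t "test or non-parametric test".
- The same paragraph adds: "Repeated-measures ANOVA using the group-by-time interaction terms will be used to analyze the between-group differences". It also mentions a multivariate analysis of variance with Bonferroni-corrected pairwise comparisons over time. Neither is tied to the normality result, and none of these analyses is ranked above the others.

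Secondary outcomes analysis carries a similar approach over to the other clinical scales (ISI, GSRS, HAMD).

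Sample size calculation bases the trial on means: 51 per group "to detect a between-group mean difference of 1.47 in treatment efficiency", which it defines as change in PSQI.

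**The concern.** A t test compares means in PSQI points. A t test after transformation compares means on another scale. A rank test compares the two distributions by ordering. If a preliminary test on the trial data determines which of these is run, the quantity estimated is not fixed in advance and may not be the one used for sizing.

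Kolmogorov-Smirnov is also poorly suited to this score. PSQI is the sum of seven components, each scored 0 to 3 (Primary outcome), so the total moves in whole points from 0 to 21. With an SD of 2 to 3 points, each step is large relative to the spread. The test can then reject because the score is discrete, which says little about whether a comparison of means is safe at 51 to 57 per arm.

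**Working it through.** **Inputs.** From Sample size calculation: post-treatment PSQI mean and SD of 8.45 and 2.06 (ARQE) and 9.92 and 2.65 (CBTI); difference 1.47; two-sided alpha 0.05; power 0.80; 51 evaluable and 57 recruited per arm. Assumed: integer totals, and scores normal before rounding.

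**The plan's own figure.** n per arm = 2(1.960 + 0.842)² × SD² / 1.47². With SD 2.65 in both arms this gives 51.0, matching the stated 51. With the two stated SDs, (1.960 + 0.842)² × (2.06² + 2.65²) / 1.47² gives 40.9, so 41. The plan therefore appears to have used the larger SD throughout. This does not affect the present point, except that power at 51 per arm exceeds 0.80 if the two stated SDs hold. 51 / 0.90 = 56.7, so 57 recruited.

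**Why rounding matters.** The largest step in the distribution of a rounded normal score is about 0.399 / SD, and the empirical curve departs from the smooth one by about half a step:

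- SD 2.06: 0.399 / 2.06 = 0.194, half = 0.097.
- SD 2.65: 0.399 / 2.65 = 0.151, half = 0.075.

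At 57 per arm the 5% critical value is about 0.117 with the Lilliefors correction (simulated). Without it, the value is 0.177 (exact) or 0.180 (asymptotic). Rounding alone uses up most of the first allowance but only about half or less of the second.

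**Rejection of normality by rounding alone** (simulated, level 0.05, scores limited to 0 to 21):

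| Version, n per arm | ARQE arm | CBTI arm | At least one arm |
|---|---|---|---|
| Lilliefors, 51 | 76–77% | 51–52% | 88–89% |
| Lilliefors, 57 | 84–85% | 58% | 93% |
| Uncorrected, 51 | 4–5% | 1–2% | 5–7% |
| Uncorrected, 57 | 5–7% | 1–2% | 6–9% |

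Unrounded normal scores give 5% per arm with the Lilliefors version, so rounding is the cause. The spread in the uncorrected rows comes mainly from asymptotic versus exact p values.

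**Variants.** Testing both arms pooled (102 to 114 scores): 93% to 100% with Lilliefors, 8% to 40% without. Testing integer change scores at 57 per arm, for which the article gives no SD, with assumed SDs of 2 to 4: 87% falling to 29% with Lilliefors, and 6% falling to 0.4% without.

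**Effect on the conclusion.** Rule simulated: t test if both arms pass, otherwise Mann-Whitney.

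| | Fixed t test | Rule, Lilliefors | Rule, uncorrected |
|---|---|---|---|
| Type I error, 51 / 57 | about 0.05 | 0.048 / 0.052 | 0.050 / 0.051 |
| Power at 1.47, 51 / 57 | 0.87 / 0.90 | 0.85 / 0.89 | 0.87 / 0.90 |

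The t and Mann-Whitney tests disagree on significance in about 2% of null trials and about 4% of trials at the design difference. Reporting whichever of the two is significant would give a type I error of about 0.06.

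**The case against.** The strongest points on the other side are these.

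- **The selection rule is not written down.** A reader might infer that the article states that Kolmogorov-Smirnov decides the test. It does not. The normality sentences lead to transformations and descriptive summaries, and the choice of test comes a paragraph later. Selection by the normality result remains the natural reading, because nothing else is offered to choose between the two.
- **The repeated-measures ANOVA is unconditional.** A reader might infer that the whole primary analysis is chosen by the data. That goes too far: the ANOVA and MANOVA do not depend on the check. The point is confined to the two-group comparison. Because the analyses are unranked, the fix has to say what becomes of the ANOVA and MANOVA.
- **Frequent rejection needs the Lilliefors version.** It is tempting to say that the check will usually reject. That is true of one version and false of the other. Which version is meant could be settled in an analysis plan that is not shown, so its absence from an article is not itself a fault.
- **The simulated scores may not match the analysed ones.** The effect is defined as a change, and non-completers are counted as unchanged from baseline. Under the 10% loss assumption this could put up to about a tenth of change scores at exactly zero. The rates above are for rounded normal post-treatment scores and are illustrative for anything else.
- **The analyst is to be blinded.** Randomization and Primary outcome analysis both say so. This limits selection for a favourable result, but it does not stop the test from depending on the data.

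**Conclusion.** The point holds in a limited form. For the two-group PSQI comparison, the article describes a normality check with transformation and a rank test as alternatives to the t test, and the natural reading is that the data determine which is used. At the planning values, discreteness alone would send about nine trials in ten away from the plain t test under the Lilliefors version, but fewer than one in ten under the uncorrected version. These rates assume integer totals, normality before rounding, and testing of post-treatment scores by arm.

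A reader might infer that this threatens the error rates. The calculations do not support that: type I error stays near 0.05, and the largest power loss is about 2 points, from a level already above 0.80 with the two stated SDs. The cost is to the estimand. The headline result may be a transformed mean or a rank comparison, neither of which estimates the 1.47-point mean difference behind the sample size. This is a cheap improvement and not a flaw that endangers the trial.

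**What to change.** Under Primary outcome analysis, remove the normality check as a condition for analysing PSQI and the other scales, together with the transformation step for those outcomes. Name one mean-based between-group comparison of PSQI as primary, to be used whatever the distribution. A baseline-adjusted comparison is preferable; otherwise use the t test already named. Label the repeated-measures ANOVA and the MANOVA as supportive. Keep a Mann-Whitney test or a bootstrap 95% confidence interval for the mean difference as a prespecified sensitivity analysis. Medians and interquartile ranges can still be reported descriptively.

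The cost is a change of wording; sample size, visits and data collection stay as they are. The only statistical downside is a small loss of efficiency if the scores turn out strongly skewed, and the sensitivity analysis would bring that to light.

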**Fig. 1 Fig1:**
[figure not shown]
Neuroimage and clinical data analysis

**Table 1 Tab1:** Schedule for enrollment, intervention, and assessment

Activity	Phase (time point)	Screening/enrolment (week0)	Allocation	Treatment/intervention								Follow-up
				Weeks 1	Weeks 2	Weeks 3	Weeks 4	Weeks 5	Weeks 6	Weeks 7	Weeks 8	Weeks 12
Enrolment	Eligibility screening	√										
	Acquisition of informed consent	√										
	Clinicopathological evaluation	√										
	Enrolment	√										
	Random allocation		√									
Treatment/intervention	Abdomen-rubbing qigong exercise			√	√	√	√	√	√	√	√	
	Cognitive behavioral therapy for insomnia			√	√	√	√	√	√	√	√	
Outcome assessment	PSQI	√					√				√	√
	ISI	√					√				√	√
	GSRS	√					√				√	√
	HAMD	√					√				√	√
Safety observation	fMRI	√									√	
	Adverse event			√	√	√	√	√	√	√	√	√
	drug combination			√	√	√	√	√	√	√	√	√

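### None of the named between-group tests adjusts for the week-0 score; ANCOVA on baseline would use the same patients more efficiently at no cost

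*Protocol article*

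**What the plan says.** The protocol article, under Primary outcome analysis, names its between-group methods. "To compare the primary and secondary outcomes between groups, continuous data will be tested by" Student's t test or a non-parametric test. The same paragraph then gives repeated-measures ANOVA with group-by-time terms as the analysis of between-group differences, and adds a multivariate analysis of variance with Bonferroni-corrected pairwise comparisons of score changes. Secondary outcomes analysis applies a similar approach to the other clinical scales. No baseline covariate appears in any of these, and the text does not say which test is the primary one.

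Table 1 ("Schedule for enrollment, intervention, and assessment") and the outcome sections place PSQI, ISI, GSRS and HAMD at weeks 0, 4, 8 and 12, so every randomised participant should have a baseline value on each scale.

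The Sample size calculation uses post-treatment PSQI summaries: for ARQE, values that "after treatment are 8.45 and 2.06", and for CBTI, values that "after treatment are 9.92 and 2.65" (mean, then SD). It nevertheless describes the target as sufficient power "to detect a between-group mean difference of 1.47 in treatment efficiency, defined as the change in PSQI score". No SD of change and no baseline to follow-up correlation is given.

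**The concern.** When an outcome is measured before randomisation, using that measurement as a covariate is the standard way to remove predictable between-patient variation from the treatment comparison. A t test on post-treatment scores leaves that variation in. A t test on change takes baseline out with a fixed coefficient of 1, which adds noise when the correlation is low. A group-by-time interaction treats week 0 as one more outcome visit and spreads the test over several degrees of freedom.

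At stake are the width of the confidence interval and the power obtained from the same 114 participants. Adjustment also removes chance baseline imbalance from the estimate. Randomization describes blocks of four and no stratification on baseline PSQI.

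The mixed description of the endpoint adds to this. If the t test is run on change, as the sample size section's wording suggests, the stated power is no longer secured by the post-treatment SDs on which it was calculated.

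**Working it through.** **Inputs from the document.** The design is set "with the two-sided significance level (α) set at 0.05 and statistical power at 0.80". Post-treatment means are 8.45 and 9.92, a difference of 1.47. SDs are 2.06 and 2.65. The stated n is 51 per group, or 57 after 10% loss, allocated 1:1.

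**Assumption.** r, the baseline to follow-up correlation, is not in the document. I use 0.3, 0.5 and 0.7, with equal SDs at baseline and follow-up and the same r in both arms.

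**Reproducing the plan's figure.** n per group = 2 × [SD × (1.960 + 0.842) / 1.47]².
- SD 2.65 in both arms: 51.01, which matches the stated 51.
- Both SDs, root-mean-square √[(2.06² + 2.65²)/2] = 2.373: 40.9, so 41, which does not match.
- Inflation for loss: 51/0.90 = 56.7, so 57.

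The stated n is therefore that of an unadjusted comparison of post-treatment scores with the larger SD in both arms.

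**Variance of the three comparisons, relative to the post-score t test**
- Post score: 1
- Change score: 2(1 − r)
- ANCOVA: 1 − r²
- ANCOVA relative to change: (1 − r²) / [2(1 − r)] = (1 + r)/2

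| r | Change | ANCOVA | Variance removed by ANCOVA (r²) | ANCOVA / change |
|---|---|---|---|---|
| 0.3 | 1.40 | 0.91 | 9% | 0.65 |
| 0.5 | 1.00 | 0.75 | 25% | 0.75 |
| 0.7 | 0.60 | 0.51 | 49% | 0.85 |

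**Power at 51 per arm, difference 1.47** (noncentral t, two-sided 0.05; the SD is multiplied by the square root of the factor above)

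| SD | Analysis | r = 0.3 | r = 0.5 | r = 0.7 |
|---|---|---|---|---|
| 2.65 | Post-score t test | 0.79 | 0.79 | 0.79 |
| 2.65 | Change-score t test | 0.65 | 0.79 | 0.95 |
| 2.65 | ANCOVA | 0.83 | 0.89 | 0.97 |
| 2.37 | Post-score t test | 0.87 | 0.87 | 0.87 |
| 2.37 | Change-score t test | 0.74 | 0.87 | 0.98 |
| 2.37 | ANCOVA | 0.90 | 0.95 | 0.99 |

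**Same gain as sample size.** By the normal formula with SD 2.65, 80% power needs 51.01 × (1 − r²) per group. That is 46.4, 38.3 and 26.0, so 47, 39 and 27, against 52 when 51.01 is rounded up.

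**Group-by-time interaction.** This needs further assumptions: four visits including week 0, equal correlation between all visits, half the effect at week 4, and the full effect at weeks 8 and 12. With SD 2.65, power is about 0.63, 0.79 and 0.96 for r = 0.3, 0.5 and 0.7. With the full effect already at week 4 it is about 0.67, 0.83 and 0.97. If half the effect is lost by week 12, it is about 0.48, 0.64 and 0.87. In all three cases it is below ANCOVA at the same r.

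**The case against.** **The plan does not ignore baseline.** A reader might infer from the t test sentence that it does. The documents do not support that. The repeated-measures ANOVA plausibly takes week 0 as one of its time levels, although these are not listed, and the sample size section speaks of change. Only a t test run on post-treatment scores would leave baseline out altogether. What stands is narrower: no named analysis uses baseline as a covariate.

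**The loss is not a fixed quarter.** One quarter of the outcome variance is r² at r = 0.5, a value found nowhere in the document. The range is 9% to 49%. With both stated SDs and r = 0.3, the gain over the post-score test is about 3 percentage points (0.87 to 0.90).

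**Nothing here is invalid.** Under randomisation, the post-score, change-score and repeated-measures comparisons are all legitimate, and omitting the covariate does not in itself introduce bias. At 51 per arm the unadjusted post-score test has 79% to 87% power on the plan's own inputs, so a reading that this choice leaves the trial underpowered is not supported. The change score falls short at r = 0.3, but the document does not say that the t test is run on change.

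**The interaction figures depend on the time course.** With an early full effect and r of at least 0.5, the interaction beats the unadjusted t test. That is correct, but ANCOVA still exceeds it.

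**This is a condensed article.** Covariates are often left to the analysis plan, which is not shown. That would carry weight if the article were silent on method. It names its tests, however, and a better one can be substituted for them.

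**Conclusion.** The point holds as a free improvement in efficiency, not as an error of validity. The named between-group analyses do not adjust for the week-0 score, which is collected for all four scales. ANCOVA has the highest power in every scenario calculated. Over the post-score t test at 51 per arm, the gain is about 4, 10 and 18 percentage points with SD 2.65, and about 3, 7 and 12 with SD 2.37, for r = 0.3, 0.5 and 0.7. Over a change score, the gain is largest where r is low: 0.83 against 0.65 at r = 0.3 with SD 2.65.

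The direction holds against a post score for any r above 0 and against a change score for any r below 1, apart from the one degree of freedom spent on the covariate. The size rests on an assumed r and on equal SDs at baseline and follow-up. The interaction figures rest in addition on the assumed time course and on equal correlation between visits.

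**What to change.** Make the between-group comparison of PSQI an ANCOVA at week 8, or the week-8 contrast of a mixed model for repeated measures, with baseline PSQI as covariate. Report the adjusted mean difference with its 95% confidence interval. Do the same for ISI, GSRS and HAMD, each with its own baseline value. Week 8 is the end of the intervention and fits the post-treatment inputs of the sample size calculation.

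The cost is a change of wording in the analysis section. The baseline values are already scheduled, the planned SPSS software fits these models, and no extra patients or visits are needed. The stated sample size can remain. The article reports that recruitment is at an early stage, so the change can be made before any outcome is compared by group.

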#### Secondary outcomes analysis

Secondary outcomes included clinical scale outcomes and neuroimage outcomes. Clinical scale outcomes will be undertaken by using a similar approach as the primary analysis.

The neuroimaging outcomes were statistically analyzed as follows: an independent *t* test will be used to compare the ALFF value and functional connection of the abdomen group, behavioral cognitive education group, and healthy control group. The two-sample *t* test will be used to compare the ALFF values between the two groups. Data of the two groups will be compared using paired *t* test before and after treatment. Select the largest peak coordinates of the different brain regions after ALFF analysis, save the clusters where the peak coordinates are located as a mask as the region of interest (ROI), and calculate the difference in functional connection between the ROI and the whole brain. The specific process is the seed area (ALFF difference brain area) is functionally connected with all voxels of the whole brain, which is the FC average image. After a correlation of values obtained from each voxel is subject to Fisher’s R-to-Z transformation, the data between groups will be subject to a two-sample *T* test and the data within the groups were subjected to paired *T* test and FWE correction. All the statistical analysis and processing will be completed independently by a research staff who has not participated in the treatment and scale evaluation throughout the entire process.

#### Interim analysis

An interim analysis will not be conducted.

#### Ethics and communication

Under the guidance of the Declaration of Helsinki’s general guidelines for medical research in humans and in accordance with local law, the study plan has been approved by the Regional Ethics Review Committee of Yueyang Hospital of Integrated Traditional Chinese and Western Medicine affiliated to Shanghai University of Traditional Chinese Medicine (Project NO. 2019-106) and registered on China Clinical Trial Registry (registration NO. ChiCTR1900028009). The standard protocol project: SPIRIT 2013 has also been observed [33]. Protocol modifications will be informed to Ethics Review Committees and the trial registry for their approval.

The results of this study will be published in a peer-reviewed journal or in the proceedings of academic conferences.

## Discussion

The purpose of this study is using the Clinical Scales and neuroimage scan to evaluate the clinical efficacy and brain function changes of the ARQE in the treatment of chronic insomnia. ARQE has sufficient theoretical basis and clinical practice experience in the treatment of insomnia. The classic Chinese traditional medicine “Huang Di Nei Jing” has the theory that “inharmonious stomach function leads to insomnia” [34, 35]. It is believed that gastrointestinal dysfunction may cause insomnia. Research has also found that gastrointestinal function and sleep affect each other. For example, patients with insomnia have abnormal digestive function, and patients with functional digestive tract diseases such as irritable bowel syndrome (IBS) and functional dyspepsia (FD) are also prone to sleep disorders [36]. Some research has also achieved good results in treating insomnia from the spleen and stomach theory. Wang’s research found that acupuncture at acupoints along the abdomen and stomach meridian of patients with chronic insomnia can relieve the symptoms of insomnia [37]. Zhang’s research found that acupuncture at local acupoints on the abdomen can relieve the clinical symptoms of patients [38].

ARQE is a treatment method mainly composed of 8 abdominal rubbing movements, which using gentle pressing to directly stimulate acupoints in the abdomen and stomach has the effect of enhancing digestive function and improving the efficacy of patients with insomnia symptoms. It has the characteristics of simple exercise method, gentle operation technique, flexible exercise time, and various postures. “Abdomen” is considered to be a specific acupuncture point for children’s massage in traditional Chinese medicine, and it is also often used in adult massage. It has the function of regulating the qi movement of the viscera and restoring the normal physiological functions of the viscera. There are a variety of internal organs in the abdomen, such as stomach, intestines, gallbladder, and pancreas. This gentle treatment can directly act on the abdomen and adjust the function of the gastrointestinal autonomic nerves by deforming and displacing the contents of the intestine, excites the intestinal parasympathetic nerves, promotes the contraction of gastrointestinal smooth muscles, strengthens peristalsis, and also promotes the secretion of gastric juice, bile, pancreatic juice, and small intestinal juice, and enhances the digestion of food by the stomach and the digestion and absorption of food by the small intestine. By improving the digestive function of patients, the symptoms of insomnia can be alleviated. In this trial, we asked patients with insomnia to perform supine ARQE before going to bed at night. This practice method helps patients relax before going to bed, reduces the time to fall asleep under gentle stimulation, and prepares the body and mind for sleep as soon as possible. ARQE, as a kind of qigong exercise, also has the characteristics of slow movement, coordination, and organic combination with breathing, which can regulate the negative emotions of patients with insomnia and change the activation of brain functions. In previous research, there is also a “brain-gut axis,” a neuro-endocrine network that connects the gastrointestinal tract and the brain through the nervous system. The central nervous system can regulate the function of the gastrointestinal tract by sending signal impulses down through the brain-gut axis [39]. Abnormal function of the gastrointestinal tract can also affect the related neural activities of the central or peripheral system including insomnia.

Chronic insomnia is a typical mind-body illness, which not only affects sleep function but also causes many other symptoms, such as mental health and digestive function. This study will evaluate the ARQE from multiple perspectives [40]. The most important thing in the treatment of insomnia patients with ARQE is to relieve the symptoms of insomnia. Therefore, in this study, PSQI and ISI scales which are most commonly used to evaluate sleep quality are selected to evaluate sleep quality and clinical effects of ARQE before and after intervention. Patients with insomnia often have some psychological and emotional abnormalities, which affect daytime function and aggravate the patient's symptoms. Therefore, HAMD will be used to assess the patients’ psychological depression. As a treatment method to treat insomnia from the spleen and stomach, we will use GSRS to reflect the gastrointestinal function of insomnia patients. We will observe changes in the gastrointestinal function of patients with insomnia before and after treatment to verify whether ARQE relieves the symptoms of insomnia by improving the gastrointestinal function and further verify the theory the theory of “inharmonious stomach function leads to insomnia”.

Neuroimage scan can reveal the changes in brain activation and functional connectivity in patients with insomnia treated by ARQE, providing clear, effective, and intuitive evidence. Previous fMRI studies have found abnormalities in multiple brain areas such as the cingulate gyrus, hippocampus, amygdala, insula, and prefrontal cortex in patients with insomnia [23]. Sleep disorders can lead to changes in the structure and function of the hippocampus [41, 42]. Patients with insomnia will experience bilateral hippocampal atrophy, involving the head, body, and tail of the hippocampus, and the size of the hippocampus is related to the length of the insomnia. In a recent study, the functional connectivity between the left hippocampus and the fusiform gyrus in patients with insomnia was weak [43]. After cognitive behavioral therapy, the functional connectivity between these altered left hippocampus and the fusiform gyrus was enhanced. These studies prove the important role of the hippocampus in the neuropathology of insomnia. Feng’s study found that after cupping intervention, the PSQI score of insomnia patients decreased the hippocampus volume increased and the brain function link between the hippocampus and the anterior cingulate cortex and the medial prefrontal cortex increased significantly [44]. Therefore, when studying ARQE, while observing the improvement of patients’ insomnia symptoms, we will also observe the correlation between the improvement of patients’ insomnia symptoms and the function of brain regions, especially the hippocampus and other important areas.

The results of this trial are expected to evaluate the efficacy of ARQE in the treatment of patients with insomnia through the degree of changes in brain activation and the related results of the clinical scale in order to confirm whether ARQE can effectively alleviate insomnia. We believe that the results of this study will provide a new solution for the treatment of insomnia for other researchers to learn from. This trial also has certain limitations. Due to the significant difference between “ARQE” and “CBTI,” blinding methods cannot be used for therapists and subjects, leading to a certain risk of bias in this experiment. Therefore, we set the same intensive training frequency to ensure the same frequency of contacting between the two groups of subjects and therapists, establish the same good doctor-patient relationship, and reduce the resulting differences. In order to ensure the authenticity of the experimental data and reduce the deviation due to the experimental process, we will strictly randomize the subjects and make the therapists, evaluators, and statisticians cannot contact each other. The neuroimaging research in this trial is only at the exploratory stage, and the sample size is limited. In future studies, the sample size can be increased to obtain more convincing evidence.

